## Abstract

**Background:**

Poststroke cognitive impairment (PSCI) is a prevalent and disabling complication following stroke, affecting critical functions such as memory, attention, language, and executive abilities. Despite the growing clinical burden, standardized and effective treatment strategies for PSCI remain limited. Acupuncture, a key modality in traditional Chinese medicine, has shown promise in improving cognitive outcomes among survivors of stroke. However, the neural mechanisms underlying its efficacy are not well understood. The default mode network (DMN), a brain network implicated in cognition and memory, has been shown to exhibit altered functional and structural connectivity in patients with PSCI. Investigating whether acupuncture modulates DMN activity may provide critical insights into its therapeutic potential.

**Objective:**

This study aims to evaluate the efficacy of acupuncture in improving cognitive function in patients with PSCI and explore its potential neurobiological mechanisms, particularly those involving changes in the DMN, using multimodal neuroimaging techniques.

**Methods:**

We will conduct a single-blind, randomized controlled trial involving 54 eligible patients with PSCI who will be randomly assigned to either an acupuncture group or a sham acupuncture control group. Both groups will receive conventional rehabilitation therapies. The intervention group will undergo standardized scalp acupuncture targeting Baihui (GV20), Shenting (GV24), and Sishencong (EX-HN1) for 8 weeks. The control group will receive sham acupuncture at nonacupoint locations using placebo needles. Cognitive function will be assessed at baseline and 4 and 8 weeks using the Montreal Cognitive Assessment and Mini-Mental State Examination. Secondary outcomes include activities of daily living, quality of life, and neuroimaging data acquired through resting-state functional magnetic resonance imaging and diffusion tensor imaging.

**Results:**

This study is currently in the recruitment phase. All results, including clinical and imaging data, will be reported upon trial completion and publication.

**Conclusions:**

This protocol is designed to investigate the efficacy of acupuncture and its underlying mechanisms in treating PSCI, with a particular focus on functional brain networks. By integrating clinical cognitive assessments and neuroimaging analysis of DMN connectivity, this study seeks to establish objective correlates of cognitive improvement. Findings from this research may advance the understanding of how acupuncture modulates large-scale brain networks and contribute to the development of imaging-based biomarkers for treatment evaluation. If successful, this approach could support the inclusion of acupuncture as a personalized nonpharmacological strategy in the neurorehabilitation of cognitive deficits following stroke.

**International Registered Report Identifier (IRRID):**

PRR1-10.2196/74981

## Introduction

### Background

Stroke stands as a prominent global contributor to disability and mortality. Annually, it afflicts 13.7 million individuals and claims 5.5 million lives [1]. Often accompanied by limb hemiplegia, aphasia, dysphagia, and other neurological dysfunctions, stroke is responsible for a high likelihood of cognitive impairment [2]. In 2016 alone, the world witnessed 13.7 million new incident strokes [3], with an annual incidence ranging from 150 to 200 per 100,000 people [4]. Poststroke cognitive impairment (PSCI) refers to a range of cognitive deficits that may develop in patients following a stroke. It can manifest as poststroke dementia, which occurs in up to a third of patients within a year after the stroke and is closely linked with increasing age [5]. The underlying pathology of PSCI is heterogeneous, with many cases stemming from various vascular etiologies and brain changes in addition to degenerative processes. PSCI encompasses conditions such as multi-infarct dementia, strategic infarct-related dementia, subcortical ischemic vascular dementia, and Alzheimer disease [6]. It emerges as a common complication, with studies reporting the combined prevalence of PSCI as 39% to 47% [7]. Three months after stroke, dementia develops in 6% to 32% of patients, elevating the risk of dementia in survivors of stroke to 3.5 to 5.6 times that of the general population. The associated cognitive dysfunction significantly diminishes quality of life for affected individuals [8]. Evidence-based medical research underscores that cognitive dysfunction exerts a more enduring impact on survivors of stroke than physical dysfunction [9], making cognitive rehabilitation a pressing research focus.

Presently, there is a lack of a standardized and effective treatment plan for PSCI, and exploration into rehabilitation methods for cognitive function continues [10]. While cognitive training is widely used and has shown positive therapeutic outcomes, its effectiveness relies on the patient’s cognitive condition, and it typically does not maintain long-term benefits [11,12]. Emerging technologies such as cranial magnetic stimulation and virtual reality hold promise, yet they remain unstandardized, their costs remain high, and widespread implementation remains challenging [13]. In contrast, traditional Chinese medicine (TCM) therapy, notably acupuncture, has gained international recognition. Numerous studies attest to acupuncture’s efficacy in treating cognitive dysfunction [14-16].

Moreover, investigations into the regulatory mechanisms of acupuncture on cognitive function have yielded insightful findings. For instance, Lu et al [17] observed that acupuncture enhances blood perfusion and glycol metabolism in specific brain regions, positively impacting cognition. Huang et al [18], using a combination of positron emission tomography and computed tomography, demonstrated that acupuncture exerts a regulatory effect on brain functional areas, potentially contributing to poststroke patient rehabilitation.

According to the principles of TCM, the brain marrow serves as the material foundation for cognitive maintenance. Kidney essence deficiency can lead to insufficient brain marrow, potentially causing cognitive decline. It may be attributed to mild cognitive impairment (MCI) induced by renovascular hypertension [19]. On the basis of previous research findings, Baihui (GV20), Shenting (GV24), and Sishencong (EX-HN1) are closely associated with improvements in brain and cognitive functions. These acupoints are commonly selected in basic research on ischemic stroke, autism, depression, and other related conditions [20,21]. The acupoint Baihui (GV20) is believed to connect the governor vessel with the brain and is closely associated with brain function. Baihui (GV20) and Touqu (GB7) acupuncture alleviates neurological deficits by reducing oxidative stress and neuronal apoptosis via the SIRT1/FOXO1 pathway [21]. Shenting (GV24), also part of the governor vessel, is described in Huang-Fu Mi’s *The*
*Systematic Classic of Acupuncture and Moxibustion* as the intersecting point of the bladder meridian of foot taiyang, the stomach meridian of foot yangming, and the Du meridian, with effects that include calming the mind and stimulating the brain, making it useful for treating mental and cognitive disorders. Sishencong (EX-HN1), an extra point located on the neck and head, is described in the *Taiping Shenghui Fang* as having the ability to tranquilize and enlighten the mind. Together, Baihui, Shenting, and Sishencong are thought to enlighten and awaken the mind of patients experiencing cognitive impairment. In recent years, acupuncture—a key modality of TCM—has gained increasing global recognition for its potential in cognitive rehabilitation. Clinical studies have reported that acupuncture may improve cognitive function in individuals with MCI, Alzheimer disease, and PSCI [16,22,23].

Neuroimaging and metabolic studies have suggested that acupuncture may exert regulatory effects on brain regions associated with cognition. For instance, Ma et al [7] conducted a meta-analysis of functional magnetic resonance imaging (fMRI) studies and found that acupuncture modulates activity in the prefrontal cortex, hippocampus, thalamus, and default mode network (DMN) in patients with MCI. Furthermore, a systematic review by Li et al [24] confirmed that resting-state fMRI studies consistently support acupuncture’s regulatory effects on intrinsic brain connectivity patterns related to cognition, attention, and memory. On the basis of both clinical efficacy and neuroimaging evidence, this study selected Baihui (GV20), Shenting (GV24), and Sishencong (EX-HN1) as the primary intervention points. These acupoints, located on the scalp overlying key cognitive and prefrontal regions, have been frequently used in previous studies on cognitive dysfunction. While TCM theory historically associates these points with mental clarity and brain function, their selection in this study is further supported by emerging neurobiological findings indicating potential roles in modulating the central nervous system.

In recent years, neuroimaging technologies have played an increasingly vital role in advancing our understanding of brain diseases. Among them, fMRI has emerged as a particularly valuable tool due to its ability to noninvasively measure brain activity and connectivity [25]. In the context of PSCI, fMRI provides high spatial resolution and can detect subtle changes in brain networks associated with cognitive processes [26,27]. Specifically, resting-state fMRI allows for the assessment of intrinsic functional connectivity without the need for active task performance—an important consideration given the cognitive and physical limitations of patients with PSCI.

The DMN, a brain network closely linked to cognition and memory, is often disrupted in individuals with PSCI [28]. fMRI enables the direct observation of DMN connectivity patterns, offering a unique opportunity to investigate how interventions such as acupuncture might modulate these networks [29]. Previous studies have demonstrated that acupuncture can influence brain activity and connectivity, including within the DMN, suggesting a potential mechanism through which acupuncture may improve cognitive function. Ellwood-Lowe et al [30] indicate that the lateral frontoparietal network and the DMN are associated with cognitive test performance. The findings of Liu et al [31] demonstrate that the functional connectivity of DMN in patients with cognitive dysfunction after stroke differs from that of healthy individuals and correlates with variations in memory function. In addition, reduced feeder and local connections have been observed within cognition-related networks, including the DMN, the salience network, the cingulate network, and the orbital network, particularly involving the caudate nucleus [32]. Notably, changes in executive function and resting-state functional connectivity are common after stroke or ischemic attacks, indicating a connection between cerebrovascular events and the prolonged impairment of neural network connectivity and cognitive function [33]. Therefore, our hypothesis posits that acupuncture might ameliorate the cognitive function of patients with PSCI by modulating the DMN. However, no studies have investigated the mechanism of acupuncture in enhancing the cognitive function of patients with PSCI from the perspective of DMN brain structure and function.

As a consequence, we are adopting a randomized controlled trial methodology for this investigation. Participants with diagnosed PSCI will be randomly assigned to either an acupuncture intervention group or a sham acupuncture group. The efficacy of acupuncture as a therapeutic modality will be evaluated through the use of standardized cognitive function scales, which will provide quantitative evidence of its clinical rehabilitative potential in enhancing cognitive function in patients with PSCI. In parallel, we will use fMRI to elucidate the neuroimaging mechanisms underlying the therapeutic effects. The objective of this research is to establish a standardized cognitive rehabilitation protocol informed by these neuroimaging insights for the treatment of PSCI.

### Objectives

The primary objective is to test the hypothesis that acupuncture, compared with conventional treatment, will lead to significant improvements in poststroke cognitive function as measured using standardized neuropsychological assessments. A secondary hypothesis is that acupuncture will modulate the functional connectivity within the DMN as detected by resting-state fMRI and that changes in DMN connectivity will correlate with improvements in cognitive performance.

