### Primary Outcomes

All practitioners involved in the study are experienced and professionally trained rehabilitation physicians or therapists. The MoCA will serve as the primary outcome measure for statistical inference as it is more sensitive to detecting MCI and changes in executive and visuospatial domains commonly observed after stroke. The MMSE will be analyzed as a key secondary outcome to provide complementary information and enable comparison with previous literature where the MMSE was the predominant tool.

Both assessments will be administered by the same trained therapist before and after the intervention to ensure consistency and minimize interrater variability. The MoCA evaluates a broad range of cognitive domains, including visuospatial and executive abilities, naming, memory, attention, language, abstraction, delayed recall, and orientation. It consists of 12 subitems, with a total score of 30 points; a score of >26 is generally considered healthy. For participants with <12 years of education, 1 point will be added to the total score to adjust for education bias.

The MMSE also provides a total score of 30 points and assesses domains such as orientation, registration, attention and calculation, recall, language, and praxis. While the MMSE is widely used in clinical settings for its brevity and utility in detecting moderate to severe cognitive impairment, the MoCA is more sensitive to subtle cognitive changes, making it more suitable as the primary statistical end point in this trial.

Multiple comparisons will be addressed by applying Bonferroni or other appropriate correction methods for secondary outcomes, ensuring statistical rigor while capturing a comprehensive and nuanced picture of cognitive changes following acupuncture intervention. The timing of treatment assessments and data collection are shown in Table 1.

**Table 1 table1:** Timing of treatment assessments and data collection.

Item			Study period				
			Before enrollment (−1 wk)	Baseline (0 wk)	Intervention period		
					4 wk		8 wk
Inclusion criteria			✓				
Exclusion criteria			✓				
Informed consent			✓				
Randomization				✓			
Allocation				✓			

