#### fMRI Scanning Scheme

A Siemens MAGNETOM Trio 3.0T magnetic resonance imager will be used for routine MRI scanning, resting-state fMRI, and diffusion tensor imaging (DTI) data collection. Both pre- and posttreatment scans will be conducted using this state-of-the-art imaging technology. For imaging data, false discovery rate correction will be used.

Conventional MRI scan sequence and parameters are as follows: (1) repetition time (TR)=600 ms, echo time (TE)=10 ms, layer thickness=5 mm, field of view (FOV)=240 mm, and matrix size=256 × 256 (T1-weighted image parameters); (2) TR=3000 ms, TE=113 ms, layer thickness=5 mm, FOV=240 mm, and matrix size=256 × 256 (T2-weighted image parameters); and (3) TR=8800 ms, TE=79 ms, layer thickness=5 mm, FOV=240 mm, and matrix size=256 × 256 (T2-weighted fluid-attenuated inversion recovery parameters).

The scanning sequence and parameters for fMRI are as follows. First, the anatomical data are collected via a T1-weighted 3D spoiled gradient–recalled sequence, and the volume images are obtained. The scanning parameters are TR=1900 ms, TE=2.26 ms, layer thickness=1 mm, FOV=250 mm, and matrix size=256 × 256. Second, the resting fMRI data are collected via real-time imaging processing. Gradient-recalled echo-planar imaging recalls the image with the following parameters: TR=2000 ms, TE=30 ms, continuous scanning of 30 layers, layer thickness=4 mm, FOV=200 mm, matrix size=64 × 64, and scanning time of approximately 8 minutes and 6 seconds.

The scanning sequence and parameters for DTI are as follows. First, the anatomical data are collected via a T1-weighted 3D spoiled gradient–recalled sequence, and the volume images are obtained. The scanning parameters are TR=1900 ms, TE=2.26 ms, layer thickness=1 mm, FOV=250 mm, and matrix size=256 × 256. Second, the DTI data are scanned through an echo-planar imaging sequence in the horizontal axis. The following parameters**―**TR=7200 ms, TE=104 ms, 49 layers, 2.5-mm thickness, number of excitations once, matrix size=128 × 128, FOV=240 × 240 mm, and 64 nonlinear diffusion gradients (b=0.1000 seconds per mm^2^)**―**are applied. The scanning duration is approximately 8 minutes and 11 seconds.

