### fMRI Preprocessing

fMRI data will be preprocessed using the DPABI toolbox a widely used open-source platform for resting-state fMRI analysis that integrates functions such as slice timing correction, head motion realignment, normalization to Montreal Neurological Institute space, spatial smoothing, and nuisance signal regression. DPABI is based on SPM12 (Wellcome Department of Imaging Neuroscience at University College London) and MATLAB (R2023a; MathWorks). Functional connectivity and amplitude of low-frequency fluctuation analyses will be conducted in this study [44].

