### fMRI Statistical Analysis

After preprocessing, statistical analyses will be conducted with *P*<.05 as the significance threshold applying false discovery rate correction for multiple comparisons. The analysis will include the following:

DMN extraction: random 2-sample *t* tests will compare extracted DMN data between groups, with *P*<.05 considered statistically significant.Functional connectivity of the DMN: the posterior cingulate cortex, medial prefrontal cortex, and medial temporal lobe were defined as regions of interest (ROIs). Resting-state functional connections between ROIs will be calculated, and the time correlation coefficient will be obtained for the 2–independent sample *t* test.Structural connectivity of the DMN: fiber bundles between ROIs will be extracted from DTI data. The average fiber bundle length (mL), average diffusion rate (MD), and mean fractional anisotropy (mFA) will be calculated for each group and compared using 2-sample *t* tests.Correlation analysis: using correlation tests, MoCA, MMSE, MBI, and Medical Outcomes Study 36-Item Short-Form Health Survey scores; *r* values; and mL, mFA, and MD values will undergo statistical analysis. The Pearson correlation coefficient (*r*) will be obtained for the *t* test.

Multiple linear regression models will be used to examine associations between groups (acupuncture vs sham acupuncture) and posttreatment cognitive outcomes (MoCA and MMSE), adjusting for baseline covariates. Logistic regression will analyze dichotomized outcomes, and interaction terms will test moderating effects of demographic and clinical variables.

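### The analysis list tests the imaging hypothesis poorly: connectivity is compared unadjusted at no stated time point, and the one named correlation sits in a grid of about 24 to 132 under an FDR of undefined scope

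*Protocol article*

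**What the plan says.** The Objectives section of the protocol article gives a secondary hypothesis in two parts. The first is "A secondary hypothesis is that acupuncture will modulate the functional connectivity within the DMN as detected by resting-state fMRI". The second is that "changes in DMN connectivity will correlate with improvements in cognitive performance". The Brand New Insights part of the Discussion also speaks of changes when it describes the correlations.

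The fMRI Statistical Analysis section sets 5% as the "significance threshold applying false discovery rate correction for multiple comparisons" and then lists:

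- t tests that "will compare extracted DMN data between groups, with" a plain 5% threshold repeated in that item;
- connectivity among three regions of interest (posterior cingulate, medial prefrontal, medial temporal), with the correlation coefficient going into a two-sample t test;
- three tract metrics from DTI, compared between groups;
- correlations of MoCA, MMSE, MBI and SF-36 scores with the connectivity and tract values.

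The fMRI Preprocessing section adds another measure: "Functional connectivity and amplitude of low-frequency fluctuation analyses will be conducted in this study". On multiplicity, the scanning section says "For imaging data, false discovery rate correction will be used", while the Primary Outcomes section says "Multiple comparisons will be addressed by applying Bonferroni or other appropriate correction methods for secondary outcomes". Imaging is itself listed among the secondary outcomes.

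**The concern.** The hypothesis is specific: connectivity, by resting-state fMRI, and its change against cognitive change. The analysis list is not. It does not say which connectivity quantity at which visit answers the first part, and it does not single out the correlation that answers the second. That correlation receives the same treatment as tract length against SF-36, which the hypothesis never mentions.

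Two things are at stake. Corrected over the whole grid, the named correlation may be missed when it is real. If FDR is instead applied analysis by analysis, the hypothesis has more than one route to a positive result. The text permits either reading, so the choice could be made after the results are seen.

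**Working it through.** **The plan's own figure.** The article gives no power or sample size for the imaging hypothesis, only 5% with FDR, so there is no calculation to reproduce. The 44 in the Sample Size section is for MoCA. It is used here only as the number of completers the plan counts on; whether it follows from its stated effect size is a separate matter.

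**Inputs**

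- n = 44 (Sample Size section).
- True correlation r = 0.40: an assumption, as the article gives none.
- Three regions, so 3 pairs, taking the medial temporal lobe as one region (assumption).
- Three tract metrics: 3 values if each is one overall average, 9 if taken per pair. The article does not say which.
- Scores: 4 scale totals, or 3 totals plus 8 SF-36 domains = 11.

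**Step 1: size of the grid, at one time point**

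- (3 + 3) × 4 = 24
- (3 + 9) × 4 = 48
- (3 + 9) × 11 = 132

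**Step 2: power for the named correlation.** If it is the only true association among m tests, it must in effect pass the strictest Benjamini-Hochberg step, 0.05/m, which is also the Bonferroni level. With Fisher's z, the expected statistic is atanh(0.40) × √(44 − 3) = 0.4236 × 6.403 = 2.713, and power = Φ(2.713 − z). The last column uses the t-based cut-off instead: r needed = t/√(42 + t²), and power = Φ((0.4236 − atanh(r needed)) × 6.403).

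| Tests m | z at 0.05/m | Absolute r needed | Power (normal) | Power (t cut-off) |
|---|---|---|---|---|
| 1 | 1.960 | 0.30 | 77% | 77% |
| 24 | 3.078 | 0.45 | 36% | 34% |
| 48 | 3.279 | 0.48 | 29% | 27% |
| 132 | 3.554 | 0.51 | 20% | 18% |

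With all 54 participants the normal figures are 86% for one test, against 40% for 48 and 30% for 132.

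**Step 3: false positives when nothing is true**

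- One FDR pool: about 5%. Simulation gave 5.1% for 64 independent tests, and 3–5% for 16 group contrasts at correlations from 0.7 down to 0.
- FDR run separately on the two analyses that address the hypothesis (DMN map and ROI connectivity): 1 − 0.95² = 9.8% if independent, 9.1% at correlation 0.5, 7.8% at 0.8.

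**Step 4: the group contrast.** Set side by side, the sections do not fix what is compared:

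- The scanning section describes scans before and after treatment. Table 1 ticks baseline, 4 weeks and 8 weeks. The t-test item names no visit.
- Regression with baseline covariates appears in the same section, but only for MoCA and MMSE.
- No Fisher transformation of the coefficients is stated.

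The value of baseline adjustment can be sketched for an assumed d = 0.40 with 22 per arm. A t test has 25% power. Adjusting for a baseline that correlates ρ with follow-up raises the effective d to 0.40/√(1 − ρ²). That is 0.46 at ρ = 0.5 (power 32%) and 0.56 at ρ = 0.7 (power 44%).

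**The case against.** The strongest reply is that this is a condensed article, that imaging is secondary and mechanistic, and that FDR families and testing details commonly go into an analysis plan that is not shown. Much of that stands. Silence on the FDR family would not be a finding by itself. What remains is that the article does fix an analysis list, and the list does not fit its own hypothesis: changes in the Objectives but not in the correlation item, baseline adjustment for the cognitive scales but not for connectivity, and one named correlation treated like every other.

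A second reply is that the power loss is a worst case. That also stands. MoCA and MMSE overlap, so a real association would probably show in more than one cell, and FDR thresholds relax when it does. The 18–36% is a floor for the pooled reading, not a forecast.

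A reader might go further and infer that DMN maps, ROI connectivity, ALFF and the three tract metrics can each confirm the hypothesis, so that the false-positive chance is several-fold: 1 − 0.95⁶ = 26% for six independent analyses. The documents do not support this. The hypothesis is limited to resting-state functional connectivity; tract metrics come from DTI and ALFF measures amplitude, so neither tests it as worded. FDR is planned in two places, and one pool holds the error near 5%. Nor does the article call this hypothesis confirmatory; it calls it secondary.

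**Conclusion.** The point holds in a limited form. As written, the plan tests its own imaging hypothesis less well than the collected data allow. The main cost is power for the named correlation: from 77% to roughly 18–36% in the worst case under pooled FDR. This rests on n = 44, a true r of 0.40, a lone true association and grids of 24 to 132 tests. False-positive inflation is small: about 5% with one pool, and about 8–10% if FDR is run separately on the two relevant analyses. The unadjusted contrast at an unstated visit is a further, avoidable loss. The primary MoCA result is not affected. For a secondary aim this is a worthwhile clarification, not a threat to the trial.

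**What to change.** In the fMRI Statistical Analysis section, name two tests of the hypothesis:

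1. The between-group difference at week 8 in Fisher-z connectivity among the three named DMN regions, adjusted for baseline. Use the mean over the pairs, or the three pairs with FDR within them.
2. The correlation of that connectivity change with MoCA change.

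Test each at two-sided 5% as secondary tests, or use a two-test Holm correction. Under Holm, the correlation faces at worst the 2.5% level, with power Φ(2.713 − 2.241) = 68% at n = 44 and r = 0.40.

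Do not make (2) conditional on (1). At the assumed d = 0.40, (1) succeeds only 25–44% of the time, so if the tests are independent, overall power for the correlation would be about 0.77 × 0.25 to 0.77 × 0.44, or 20–34%. That gives back most of the gain.

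Label DMN maps, ALFF, tract metrics and all other correlations exploratory, with FDR within them.

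The cost is one paragraph and no new data; the Results section says that nobody was enrolled as of August 2025. The downsides are that tract and ALFF results become exploratory, and that averaging over pairs could mask opposite changes. Keeping the pairs separate avoids the masking but turns (2) into three correlations, with 63% power at the strictest step (0.05/3).

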**Limitations and Future Directions**

While the randomized controlled trial and blinding methodologies are upheld, the feasibility of achieving total blindness has been acknowledged as challenging, particularly in nondrug trials. Given the unique nature of acupuncture treatment, a double-blind procedure is not feasible, leading to the decision to blind outcome evaluators and statistical analysts. In addition, both groups receive conventional cognitive training to ensure ethical equivalence; however, this may reduce the contrast between groups. Moreover, we acknowledge the limitations in generalizability of our study findings, primarily due to the single-center design and the constraints imposed by resource-intensive research protocols and the standardization of millimeter-level interventions. To minimize potential biases, we have implemented rigorous quality control measures. For future research, we plan to conduct multicenter trials to quantitatively assess general applicability and conduct additional real-world validation to further enhance the generalizability of our findings.

In summary, by adopting a multimodal neuroimaging approach, this study delves into the impact of acupuncture on the brain structure and function of patients with PSCI. By examining correlations with changes in cognitive function, this study aims to clarify the specific targets and mechanisms through which acupuncture enhances cognitive function. The findings are anticipated to yield reliable imaging markers for evaluating the efficacy of acupuncture and prognosis of PSCI, offering valuable clinical applications. If this study demonstrates a significant intervention effect, it will contribute robust evidence supporting acupuncture’s ability to ameliorate cognitive dysfunction in patients with PSCI, providing insights into its neuroimaging mechanisms.

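### The planned DMN–cognition correlation cannot by itself separate acupuncture's mechanism from change common to both arms, and nothing ties the mechanism reading to the between-arm DMN comparison

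*Protocol article*

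**What the plan says.** All references are to the protocol article.

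- **Objectives.** The secondary hypothesis has two limbs. The first is that "acupuncture will modulate the functional connectivity within the DMN as detected by resting-state fMRI". The second is that "changes in DMN connectivity will correlate with improvements in cognitive performance". The second does not mention arm.
- **fMRI Statistical Analysis.** The first limb is tested by two-sample t tests between the arms, on extracted DMN data and on connectivity between regions of interest; fibre measures are compared in the same way. For the second limb, scale scores are correlated with connectivity and fibre values: "The Pearson correlation coefficient (*r*) will be obtained for the *t* test". No arm term, split by arm or mediation model is stated. The regressions described afterwards relate arm to MoCA and MMSE, and their "interaction terms will test moderating effects of demographic and clinical variables"; a DMN term is not mentioned.
- **Brand New Insights.** The correlation is described as one between changes in DMN and cognitive function, again without reference to arm.
- **Limitations and Future Directions.** The reading is given here: "By examining correlations with changes in cognitive function, this study aims to clarify the specific targets and mechanisms through which acupuncture enhances cognitive function".
- **Background.** DMN connectivity in patients with cognitive dysfunction after stroke is reported, with no acupuncture involved, as one that "differs from that of healthy individuals and correlates with variations in memory function".
- **Eligibility Criteria; Cognitive Function Training.** Disease duration must exceed one month, with no stated upper limit. Both arms receive 30 minutes of cognitive training, five days a week for eight weeks.

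**The concern.** A correlation between DMN change and cognitive change, taken over all patients, shows that the two move together. It does not show what moved them. Patients at different stages of recovery, or responding differently to the training that everyone receives, could show linked changes in both measures in either arm. The sham arm is the reference that would separate this from an effect of acupuncture, but the correlation as described does not use it.

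The exposed result is a significant correlation without a between-arm difference in DMN change. The plan has no rule for reading it, and the sentence in the Discussion invites reading it as acupuncture's mechanism. The primary MoCA comparison is not affected; what is at stake is the mechanistic conclusion and the imaging markers that the article hopes to derive from it.

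**Working it through.** **Inputs from the article.** Evaluable sample 44 (22 per arm) and total sample 54 (27 per arm), from Sample Size; two-sided 5% level. The article gives no expected size for the DMN–cognition correlation and no calculation for it, so there is no figure of its own to reproduce here.

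**Assumption.** Acupuncture affects neither DMN change nor cognitive change. The two changes have the same correlation ρ in both arms because of shared recovery or training. The documents give no value for ρ, so a range is shown. If one recovery factor explains a share R² of the variance of both changes, then ρ = √R² × √R² = R².

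**Pooled correlation, Fisher z approximation.** With δ = atanh(ρ) × √(n − 3), the chance of significance is Φ(δ − 1.96) + Φ(−δ − 1.96). For ρ = 0.2 and n = 44: atanh(0.2) = 0.203, √41 = 6.40, δ = 1.30, chance = Φ(−0.66) + Φ(−3.26) ≈ 0.255. For ρ = 0.3 and n = 54: atanh(0.3) = 0.310, √51 = 7.14, δ = 2.21, chance = Φ(0.25) ≈ 0.60. Simulation with 20,000 trials per setting agrees:

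| Assumed ρ | Pooled correlation significant, n = 44 | n = 54 | Between-arm t test on DMN change significant |
|---|---|---|---|
| 0.1 | 10% | 11% | 5% |
| 0.2 | 25–26% | 31% | 5% |
| 0.3 | 51–52% | 60–61% | 5% |

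Where a range is shown, it is the spread between separate simulation runs. The article places its imaging analyses under false discovery rate correction; the table uses the unadjusted 5% level.

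**Both limbs together.** At ρ = 0.3, the correlation and one between-arm DMN test are both significant in about 2.6% (n = 44) to 3.0% (n = 54) of these null trials. With ρ up to 0.5 the figure reaches at most 4.8%. The correlation without the between-arm difference at ρ = 0.3 therefore occurs in about 51.5% − 2.6% = 49% (n = 44) to 60.1% − 3.0% = 57% (n = 54).

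**What adjustment achieves.** Under this null, arm is unrelated to either change, so adding arm leaves the rate almost unchanged at ρ = 0.3: about 51–52% (n = 44) and 60–61% (n = 54). Adjusting for the true recovery factor returns it to 5%, but that factor is not observed. Suppose instead that time since stroke shares an assumed 30% of variance with it. The correlation of each change with this proxy is then √0.30 × √0.30 = 0.30, and the partial correlation is (0.30 − 0.30 × 0.30) / (1 − 0.30²) = 0.21 / 0.91 = 0.23. With arm and the proxy in the model, δ = atanh(0.23) × √(n − 5), which gives about 31% (n = 44) to 38% (n = 54). Simulation gave 32% and 39%.

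**The case against.** A reader might infer that the whole mechanism objective rests on the correlation, so that the trial could declare a mechanism under a complete null. The documents do not support that. The hypothesis joins two limbs, and the first is tested between randomised arms. If acupuncture did nothing, that test is positive about 5% of the time before correction, and both limbs together at most about 5%. The last sentence of the Discussion also makes its claim of robust evidence conditional on a significant intervention effect, and Brand New Insights describes the correlation only as showing neuroimaging correlates.

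A reader might also take it as established that spontaneous recovery produces the correlation. It is not. The article gives no size for it; the Background finding concerns variation between patients, not eight-week change; and symptoms must be nonprogressive with no upper limit on duration, so patients with little remaining recovery may enter. At ρ = 0.1 the inflation is modest.

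Finally, a condensed article may leave reporting by arm and covariates to the full protocol or analysis plan, and false discovery rate correction is stated.

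The first two replies narrow the point and stand. The rest does not remove it. The stated condition is an intervention effect, not a DMN difference: a MoCA benefit, a correlation and no between-arm DMN difference would still fit the mechanism sentence. False discovery rate correction limits chance findings; it does not remove a genuine correlation with another cause. And the point does not rest on missing detail, because the article states both a method and a reading, and the reading does not follow from the method.

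**Conclusion.** The concern holds in limited form. The correlation limb cannot by itself distinguish acupuncture's mechanism from change common to both arms, yet the Discussion says that the correlations will "clarify the specific targets and mechanisms through which acupuncture enhances cognitive function", and no section makes that reading conditional on the between-arm DMN result. With no acupuncture effect, the pooled correlation would be significant in about 10% of trials at an assumed ρ of 0.1, 25–31% at 0.2 and 51–61% at 0.3, for 44 to 54 patients at an unadjusted 5% level; the between-arm DMN test stays near 5%. These rates depend on ρ, which is an assumption. The logical gap does not. This should be changed, but it bears on a secondary conclusion and leaves the primary MoCA analysis as it is.

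**What to change.** 1. State that a mechanism reading requires a between-arm difference in DMN change as well as a DMN–cognition association. This is the main safeguard.
2. Estimate the association by regressing MoCA change on DMN change with arm and time since stroke in the model, and show it by arm. Label the arm × DMN change interaction as exploratory.
3. If only the correlation is seen, report it as a correlate of cognitive change, not as acupuncture's mechanism. Reword the mechanism sentence in Limitations and Future Directions to match.

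The adjustment in step 2 should not be relied on alone: adjusting for arm removes only correlation induced by differences in arm means, and time since stroke is an imperfect proxy for recovery.

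The cost is confined to analysis and wording. The imaging and MoCA data are already planned; time since stroke has to be recorded as a value, which the duration criterion at entry should already make available. The mechanism claim becomes harder to reach, and one or two degrees of freedom are used.
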